### Waiting list

Participants allocated to the waiting list group are asked to avoid chiropractic treatment or SM by any other provider within or outside the military health system during the active trial period. Participants in this group are scheduled for one additional visit 4 weeks (±7 days) after allocation. Waiting list group participants may receive any other care available to them. All treatment obtained for LBP during this trial is documented via participant self-report and confirmed through review of their military medical record. After trial completion, waiting list group participants are offered the option to be scheduled for CC. Care provided beyond this time is not part of the trial and no data are collected. During weeks 1–3, the PM contacts each participant (both groups) weekly to track treatments for LBP and to screen for adverse events.

### Final visit

The final visit is conducted 4 weeks (±7 days) from allocation. It begins with another safety check prior to testing. Participants then complete PROs by logging into STaRS on the dedicated trial computer. Balance, strength, and endurance tests are performed next. At the end of the visit, participants are thanked for their participation and waiting list group participants are offered the option to receive CC. For those who desire care, the PM facilitates contact with the chiropractic clinic for scheduling.

### Outcome measures

The primary outcome for this trial is a change in strength following the 4-week active period. Strength was chosen as the primary outcome because it is the muscular function most fundamentally necessary for balance and endurance. Preliminary data were also available to the study team after conducting an unpublished pilot study with the strength test used in this trial. Secondary outcomes include changes in balance and endurance and PROs. Figure 2 displays the schedule of events including the data collection schedule for the primary and secondary outcomes.

**Fig. 2 Fig2:**
[figure not shown]
Schedule of events

### Strength

The strength test involves isometric pulling on a bimanual handle while in a semi-squat position, similar to a test described by da Silva and colleagues [40]. The handle is attached to a chain connected to a height-adjustable support anchored to the floor. The chain connecting the handle to the anchored support contains a force transducer (FSH00080, FUTEK Advanced Sensor Tech, Inc., Irvine, CA). The height of the handle is determined by the participant’s patellar height and set by the PM to ensure standardized positioning within and across participants (Fig. 3).

**Fig. 3 Fig3:**
[figure not shown]
Strength test. Isometric pulling in a semi-squat position with upright torso and eyes facing forward. Foot position is standardized within participants using platform markings (**a**). The bimanual handle (**b**) is attached to a force transducer. Pulling height is standardized using an adjustable post accommodating variable participant height (**c**)

Participants wear a harness allowing free movement of the arms, legs, and torso to prevent an accidental fall. While performing the test, participants are instructed in a stepwise manner to assume a proper lifting position with feet comfortably spread, knees bent, upright spine, arms perpendicular to the floor while holding the lift handle, and eyes looking straight ahead.

Participants are instructed to pull first with a self-monitored light force to confirm they are in the right pulling position and to assess for increased pain. Pulling occurs for less than 5 s with a gradual release of pressure to end the test. Participants are instructed to stop pulling if any increased discomfort is experienced. If the light pull is successfully accomplished without increased discomfort, participants pull again with a self-monitored medium force. If this occurs without increased discomfort, a maximum-effort pull test is attempted. The maximum pulling force is recorded in pounds (lbs.); 4.45 newtons equals 1 lb. If the final pull is halted before reaching the maximum effort, the highest (peak) pulling force is used for the data analysis.

During the maximum pull test, participants are instructed to increase the pulling force gradually up to their maximum without increasing discomfort. The maximum pull procedure is repeated three times with a minimum 2-min rest period and a voluntary warm-up guided by the PM before each test. The warm-up consists of walking within the room, gently bending and twisting the trunk, practicing the semi-squat lifting position, and performing light knee raises and heel kicking motions. The warm-up lasts approximately 3 min. The maximum pulling force recorded is used for data analysis. The stance width for this test is determined by allowing the participant to select the most comfortable position. The handle height is set at 2 in. above the superior aspect of the patella (kneecap). For consistency, the stance width and lifting handle height are recorded during the first assessment and applied at the following assessment. Data are collected and saved to a text file (ASCII format) and converted to Microsoft Excel. The PM saves the test file with the proper identifiers and then uploads it to the secure web system.

### Balance

To minimize potential carryover effects from the strength or endurance tests, the balance test is performed first. The one-leg standing test is an assessment of postural stability [41]. To prevent the remote possibility of falling, participants wear a safety harness that allows free movement of the arms, legs, and torso. Participants perform this test without shoes.

First, participants are allowed to practice the balancing position by placing both hands on the iliac crest region. Their dominant kicking foot is placed against the supporting leg below the knee (Fig. 4). Raising the heel of the supporting foot completes the balance position. The test commences when the heel is raised from the floor. A sensor pad under the heel activates a computer timer. The timer stops when either the heel of the supporting foot or any part of the other foot touches the floor. The balance test is repeated three times with eyes open and then three times with eyes closed. The longest holding time, recorded in milliseconds, under each condition is used for data analysis [41]. Data including appropriate identifiers (e.g., ID, test date, etc.) are saved in a text file (ASCII format), copied into Microsoft Excel, and uploaded to STaRS.

**Fig. 4 Fig4:**
[figure not shown]
Balance test. Test performed with eyes open and with eyes closed. Pressure sensitive pads (**a**) are connected to a computer timer. Lifting the heel (**b**) removes the pressure, which starts the timer. Touching any pad with either foot stops the timer and ends the test

### Endurance

The Biering-Sorensen test is an assessment of trunk muscle endurance used as an outcome measure in clinical and research settings because of its low cost, safety, reliability, and ease of use. The test is performed efficiently with minimal specialized equipment [42, 43]. As displayed in Fig. 5, participants lie face down on a padded table. The head, shoulders, and trunk extend over the edge of the table. Initially, they support themselves by resting their forearms and elbows on a padded cushion. The lower extremities are strapped to the table with wide straps as firmly as comfort will allow at the upper thigh and slightly above the ankles. Participants lift their arms off the support and maintain a neutral trunk position for as long as possible. The test ends if pain or discomfort is experienced, if the neutral trunk posture is not maintained, or when the test reaches 180 s. The holding time is recorded in seconds with a handheld stopwatch. The reason for ending the test is also recorded (e.g., discomfort, fatigue, time limit, etc.). Because this test induces trunk, pelvic, and thigh muscle fatigue, it is performed after the balance and strength tests. The test time is recorded on the testing checklist and submitted to STaRS.

**Fig. 5 Fig5:**
[figure not shown]
Endurance (Biering-Sorensen) test. **a** Head, shoulders, and trunk extend over the edge of a table. The lower extremities are strapped to the table. **b** Timing begins when the participant lifts their arms off the support stool while maintaining a neutral trunk position. The test ends if pain or discomfort is experienced or after a maximum of 180 s.

### Patient-reported outcomes

All PROs are collected at BL2 prior to baseline testing (except global improvement) and group allocation. All PROs, except expectation of care, are collected again at the final visit. Pain severity is collected using an ordinal 11-box numerical rating scale (0 = no pain to 10 = worst imaginable pain) for the worst and average levels of LBP over the past 24 h [44]. LBP-related disability is collected using the Roland Morris Disability Questionnaire, a reliable and validated single-page questionnaire commonly used in clinical research [45, 46]. The bothersomeness of symptoms of LBP during the past week is measured using an existing six-question instrument with a 1–5 scale (1 = not at all bothersome to 5 = extremely bothersome). Bothersomeness questions have good internal consistency, construct validity, and responsiveness to change over time in patients with LBP and sciatica [47, 48].

PROMIS-29 is a set of short forms containing measures of depression, anxiety, physical function, pain interference, fatigue, sleep disturbance, and satisfaction in social roles [49]. Each of the seven topic domains contains four questions. With an additional pain intensity rating, there are 29 questions in total. Perceived LBP improvement is assessed with a single question adapted from a study of expectations of acupuncture and massage among patients with LBP [50]. Perceived global improvement is rated on a seven-point Likert scale with anchors “completely gone” to “much worse” [51]. Five questions asking about physical activity outside job duties are also asked.

Most PROs measure different aspects of clinical improvement. Two additional measures collected in this trial identify factors that could potentially influence performance on the strength, balance, or endurance tests. The Fear-Avoidance Beliefs Questionnaire is a 16-item validated instrument measuring back-pain fears on two subscales related to physical activity and work. Ratings span from 0 (completely disagree) to 6 (completely agree) [52–54]. Because expectation can contribute a significant non-specific effect [50], all participants answer two questions about their expectation of the benefit of CC and the overall improvement over the next 4 weeks prior to allocation.

### Data collection and management

#### Data collection

Data are collected at each stage of recruitment, allocation, and throughout treatment, to ensure reporting according to the Consolidated Standards of Reporting Trials guidelines [55]. We collect recruitment source, total number of responses per recruitment source, the disposition of each potential participant (i.e., screening failure, ineligible, does not wish to participate, or allocated), the number allocated, participant compliance to treatment protocol, the number lost to follow-up, and the number of participants completing the trial.

Electronic data capture through STaRS occurs via unique login credentials for each user. Login credentials designate and direct access to the appropriate application areas within STaRS. PMs enter BL1 and BL2 data into customized logic-based electronic forms with embedded validation checks to ensure eligibility status prior to allocation. PRO data collected at BL2 and the final visit are entered into STaRS. Balance and strength test data are recorded electronically and uploaded to STaRS. Endurance test data are recorded on paper forms and transcribed to STaRS.

The Office of Data Management at the PCCR serves as the data coordinating center. STaRS is an integrated participant database and permissions system controlling individual access to web modules. STaRS is programmed to support data and project management and includes full technical support. It has procedures for data security, data quality control, storage, and back-up. STaRS includes modules for baseline screening; eligibility checks; treatment allocation; participant tracking; generating reports; and data file transfers for the balance, strength, and endurance tests. Uploaded files are downloaded by the data core manager and stored on a secure server at the PCCR.

All data are stored on a secure internal server running Microsoft SQL Server. STaRS resides on a production web server (IIS V10.0) secured with Secure Sockets Layer (SSL) 256-bit encryption. The system is maintained by the Palmer College of Chiropractic Information Technology department. Select personnel from the Office of Data Management have access to the SQL tables via a Microsoft SQL Server Enterprise Manager interface. STaRS is programmed in ASP.NET v4.0 in C# and SQL using Microsoft Visual Studio 2010. Servers reside behind a stateful firewall. To perform the data cleaning procedures, the data core manager will perform a soft database lock (Microsoft SQL server) and use programs written in SAS System for Windows (Release 9.4) using SAS ACCESS. After all data have been collected, and edits are recorded and performed, a final database lock will be implemented, removing all update access to the database. Final datasets for analysis and the data dictionary will be created by the data core manager, who will write and test SAS programs from the final locked database.

Paper forms containing participants’ names (informed consent documents) and data collection forms containing unique trial ID numbers are stored in locked filing cabinets accessible by the PM. At trial completion, informed consent documents will be stored at NHP for 6 years. Paper data collection forms will be transferred to the PCCR and stored in a secure room for up to 7 years.

### Statistical methods

We will use an intention-to-treat approach in which participants with non-missing data will be analyzed according to their assigned treatment. We will use SAS version 9.4 (SAS Institute Inc., Cary, NC) for data analysis. We will calculate descriptive statistics for baseline characteristics and for maximum strength, balance, endurance, and PROs at baseline and week 4 for both groups. Changes in outcome variables from baseline to week 4 will be analyzed with an analysis of covariance (ANCOVA), adjusting for the baseline value of the respective outcome variable centered at its mean and other covariates that are not balanced between groups. The group mean changes and between-groups differences in mean change based on the ANCOVA will be reported with 95% confidence intervals.

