### Sample size

We conducted a power analysis using Proc Power in SAS for our primary outcome variable, maximum strength. We used the standard deviation of 48 lbs. observed in our pilot study and assumed that maximum strength will remain unchanged in the waiting list control group. A total sample size of 82 participants, with 41 per group, provides 90% power to detect at least a 20% difference in mean change between groups at a 0.05 level of significance. In another clinical trial conducted by the investigative team at this site, we observed 23% missing data at week 2 and 29% at week 4 [56]. Therefore, we increased the sample size to 110, with 55 per group, to account for the possibility of a 25% dropout rate.

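### The primary ANCOVA lets chance baseline imbalance pick its extra covariates; a short pre-named prognostic set would be more precise and would fix the model in advance

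*Protocol article*

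**What the plan says.** The protocol article, Statistical methods, sets one ANCOVA model of the week-4 change for all outcomes. Its covariate rule reads: "adjusting for the baseline value of the respective outcome variable centered at its mean and other covariates that are not balanced between groups". The only covariate named in advance is the baseline value of the outcome being analysed. The analysis set is those for whom "participants with non-missing data will be analyzed according to their assigned treatment".

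Under Allocation, assignment is 1:1 from a computer-generated sequence in random blocks, with no stratification factor named. The same section says that data analysts and the PI are blinded to group.

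Under Patient-reported outcomes, the article says: "Two additional measures collected in this trial identify factors that could potentially influence performance on the strength, balance, or endurance tests". These are the Fear-Avoidance Beliefs Questionnaire and the expectation questions, both collected before allocation.

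Under Sample size, the calculation arrives at 82 (41 in each arm) and uses no covariate. The article says that this number "provides 90% power to detect at least a 20% difference in mean change between groups at a 0.05 level of significance".

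**The concern.** Under a random sequence, a baseline difference between the arms is chance by construction. Whether a covariate is worth adjusting for depends on how well it predicts week-4 change in strength, and observed imbalance does not measure that. An imbalance rule can therefore go wrong in two ways. It can bring in a variable unrelated to strength because the arms happen to differ on it, and it keeps out a strong predictor because the arms happen to agree. The two measures that the article itself singles out as possibly affecting test performance enter only if they are imbalanced.

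The rule also leaves the primary model open until group-wise baseline data have been inspected. At stake are the precision of the primary estimate and its 95% confidence interval, and the assurance that the model was settled before anyone could compare the groups.

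This is a stated selection criterion. A later SAP that added a candidate list and a cut-off would refine it, but would still select on imbalance.

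**Working it through.** **Inputs from the protocol article, Sample size:** SD ("We used the standard deviation of 48 lbs. observed in our pilot study"), 41 per group, 90% power, alpha 0.05, 25% dropout. **Assumptions:** a two-sided test; 48 lb taken as the residual SD of the planned model (the article does not say what this SD is of); R² = share of that variance explained by one further covariate, 0.05 to 0.30; six candidate covariates; a covariate is added when its between-group t-test gives p<0.05. The article gives none of these.

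**1. The plan's own figures.**
- Inflation: 82/(1 − 0.25) = 109.3, so 110. This matches "we increased the sample size to 110, with 55 per group, to account for the possibility of a 25% dropout rate".
- The 82 cannot be rebuilt forwards, because the mean to which the 20% refers is not given. Backwards: SE = 48 × √(2/41) = 10.60 lb. With 80 degrees of freedom, 90% power needs a noncentrality of 3.28, so Δ = 3.28 × 10.60 = 34.8 lb. That is 34.8/48 = 0.725 SD, with an implied reference mean of 34.8/0.20 = 174 lb. The steps below use Δ = 34.8 lb.

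**2. What a pre-named covariate would add.** Residual SD = 48 × √(1 − R²), same noncentral-t power at 41 per group; n for 90% power ≈ 41 × (1 − R²).

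| R² | residual SD (lb) | power | n per group for 90% |
|---|---|---|---|
| 0 | 48.0 | 90.0% | 41 |
| 0.05 | 46.8 | 91.4% | 39 |
| 0.10 | 45.5 | 92.7% | 37 |
| 0.20 | 42.9 | 95.2% | 33 |
| 0.30 | 40.2 | 97.2% | 29 |

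**3. What the imbalance rule delivers.** Simulation with N = 82, six independent covariates of which one is prognostic, and 4,000 replicates per cell (Monte Carlo standard error about 0.5 points at 90% and 0.3 points at 5%).

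| R² | power, no extra covariate | power, imbalance rule | power, pre-named | type I error, imbalance rule |
|---|---|---|---|---|
| 0.10 | 90.4% | 90.4% | 92.9% | 5.1% |
| 0.20 | 89.4% | 89.4% | 94.8% | 5.1% |
| 0.30 | 90.5% | 91.2% | 97.1% | 4.1% |

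Pre-named minus imbalance rule: 2.5, 5.4 and 5.9 points. The rule performs like no extra adjustment because the prognostic covariate enters in only about 5% of trials, which is the trigger rate.

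**4. How often chance alone changes the model.** With k independent candidates at p<0.05, P(at least one flagged) = 1 − 0.95^k: 23% for k = 5, 40% for k = 10, 54% for k = 15.

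**5. What a fixed set costs if it is badly chosen.** Each covariate uses one degree of freedom and slightly inflates the variance of the treatment estimate. Averaging noncentral-t power over simulated covariate values at N = 82 and Δ = 34.8 lb, with none prognostic: 88.9% with three covariates and 88.4% with four, against 90.0%. With four covariates of which one is prognostic: 91.4% at R² = 0.10 and 95.4% at R² = 0.25.

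**The case against.** The strongest reply is that nothing planned is lost. The article claims 90% power without any extra covariate, and the rule delivers about 90%. Usually the best single predictor, the baseline outcome, is already in the model. Retention is also better than planned: Challenges and Trial status report 93 allocated and 6.1% withdrawn or dropped out, so about 93 × 0.939 = 87 completers if that rate holds, before further enrolment. All of this stands, and it limits the point to forgone precision.

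A reader might infer more, and the documents do not support it:
- **Inflated error or an interval that is too narrow.** Selection uses baseline data and group, not outcomes, and simulated type I error is nominal or slightly low. Error would rise only if someone tried several cut-offs and kept the favourable result, which nothing in the article suggests.
- **An underpowered trial.** An effect of 0.6 SD gives only 76.5% power at 41 per group before any covariate enters, but the article's own figures imply 0.725 SD.
- **A different covariate set for each outcome.** Balance of a covariate does not depend on the outcome analysed; only the baseline value changes, apart from differences in missing data.
- **The missing list and cut-off as a defect in themselves.** A condensed article may leave these to the SAP. The criterion of imbalance is what it fixes badly.

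Blinding of analysts is a real safeguard, but a partial one: balance can be judged only by comparing the groups, even if coded, and the model is then chosen with that comparison in view. The article says only that the two measures could affect performance; it gives no evidence of their prognostic strength.

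**Conclusion.** The point holds as a matter of efficiency and pre-specification, not validity. Chance imbalance is the wrong criterion for choosing covariates, and it leaves the primary model undetermined until the groups are compared. At the article's own planning point, the rule keeps about 90% power and a type I error of about 4 to 5%. It forgoes about 2 to 6 power points if one pre-named covariate explains 10 to 30% of the residual variance beyond the baseline outcome, and nothing if none is prognostic. These sizes rest on the assumed R², a p<0.05 trigger, six independent candidates, a two-sided test and 48 lb read as the residual SD. This should be fixed, because it is a cheap improvement, but it does not threaten the trial's conclusion.

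**What to change.** Before unblinding, remove the part of the sentence under Statistical methods that adds covariates found to be unbalanced. Keep the baseline value of the outcome and name a short fixed set of prognostic covariates that the trial already collects. Age, baseline average pain and the fear-avoidance score (stating which subscale) would be one example. Sex or LBP duration class should be included only if recorded: the article mentions demographic information without listing sex, and acute, subacute or chronic pain appears only as an eligibility description. The final choice is the sponsor's, on prognostic grounds.

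Use the same set for strength, balance and endurance whatever the observed balance, and report any imbalance-driven model as a labelled sensitivity analysis.

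The cost is one sentence, no new data and three or four degrees of freedom: between 1 and 2 power points if none of the covariates turns out to be prognostic.
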